## Abstract

**Aims:**

Heart transplantation (HTX) is the treatment of choice for advanced heart failure. Still, long‐term survival needs to be improved. Recent studies showed that obesity and type 2 diabetes (T2D) as well as impaired renal and liver function are associated with mortality post‐HTX. There are many open questions including (i) optimal metabolic surveillance post‐transplant, (ii) association of metabolic deterioration and cardiac function, (iii) association with hepatic and renal deterioration, and (iv) optimal timing and choice of treatment. The METAB‐HTX trial will address these open questions, hypothesizing that metabolic deterioration post‐HTX is associated with impaired cardiac function and survival.

**Methods and results:**

METAB‐HTX is a prospective, longitudinal cohort study, enrolling 400 patients post‐HTX in a period of 5 years. Time‐series, deep cardiac, and metabolic phenotyping will be conducted. Cardiac function will be analysed by echocardiography as well as serial cardiac magnetic resonance imaging and spectroscopy (cMRI/MRS). Coronary angiography will be conducted to assess both macrovascular and microvascular coronary allograft vasculopathy (CAV). To evaluate allograft rejection, endomyocardial biopsies will be taken. Metabolic alterations will be investigated by (i) glucometabolic phenotyping including serial oral glucose tolerance tests, homeostasis model assessment, T2D endotyping, and muscle biopsies in selected cases; (ii) lipid disorders will be evaluated by classical lipid measurements in combination with evaluation of HDL function, plasma membrane lipid composition, fluidity analyses of circulating cells and MRI/MRS for adipose tissue distribution, and ectopic fat analysis. Kidney and liver function and structural alterations will be evaluated. Complex analyses will be conducted to evaluate (i) myocardial substrate utilization and energy metabolism by cardiac and circulating cell respirometry, (ii) impact of genetic (including immunogenetic) and transcriptomic factors by third‐ and fourth generation sequencing (short‐ and long‐read sequencing), (iii) circulating signatures of future neoplasia by single‐cell sequencing of circulating leucocytes, and (iv) evaluation of thromboinflammation in association with heart transplant events. The primary endpoint will be the incidence of heart transplant events, defined as worsening of systolic or diastolic left ventricular function, CAV, allograft rejection, worsening of kidney function, metabolic liver disease, infections, neoplasia, deterioration of glucose and lipid metabolism. Secondary outcomes include hospitalizations related to primary endpoints, re‐HTX or ventricular assist device, cardiovascular mortality, and all‐cause mortality.

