### Study endpoints

The primary and secondary endpoints are summarized in *Figure*
*1*. Definitions of individual heart transplant event components are:

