Glucometabolic disease will be defined as (i) impaired glucose tolerance (2‐h glucose levels of 140–199 mg per dL on the 75‐g oral glucose tolerance test), (ii) impaired fasting glucose (fasting plasma glucose values of 100–125 mg per dL), or (iii) diagnosis of T2D according to current criteria of the American Diabetes Association.^12^

Lipid disease is defined as (i) elevating low‐density lipoprotein concentrations, apolipoprotein B concentrations, and fasting triglyceride levels; (ii) impaired HDL function; (iii) enhanced membrane fluidity; or (iv) membrane cholesterol enrichment in time‐series analyses.

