### Sample size calculation

This study will prospectively include all new transplanted HTX recipients at our centre. We estimate 50 new transplantations per year. Additionally, we aim to recruit previously transplanted patients currently receiving follow‐up care at our centre. This cohort consists of 250 living HTX recipients. Based on an expected participation rate of 90%, we anticipate enrolling approximately 270 patients in the first year of the study. To address the initial hypothesis of the trial, metabolic deterioration post‐HTX is associated with impaired cardiac function and survival.

Based on previous studies, this sample size will yield a sufficient number of outcome events during the follow‐up of at least 100. Exact events rates based on glucometabolic disease are difficult to estimate from previous studies in this highly selected population, as neither glucometabolic disease nor respective outcomes have been as systematically or extensively screened for in previous trials. Thus, we estimate that, with a sample size of 400, at an alpha level of 0.05, assuming that 60% of patients develop glucometabolic disease after HTx and further assuming that the hazard for the primary outcome events is 35% higher (hazard ratio 1.35) in patients with glucometabolic disease, the estimated power for this study would be 0.8090 which is above the target of 0.8.

Beyond that, the trial is designed to allow further sub‐studies and even nested RCTs to address the aim of the study to achieve an in‐depth analyses of the interaction between metabolism, cardiac function, and inter‐organ communication and to reveal and test novel therapeutic regimens.

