
Regarding hepatic disease, we have shown that MASLD is associated with insulin resistance and impaired mitochondrial efficiency and cardiac function after acute myocardial infarction.^39^ This goes in line with clinical data associated hepatic function and mortality post‐HTX.^61^ Hence, this will be closely monitored in METAB‐HTX as well. We have a long‐lasting experience with novel cMRI sequences and methods. Recently, we revealed quantitative assessment of inflammation using fluorine imaging.^62^ cMRI is promising in post‐HTX surveillance.^63^, ^64^ Therefore, serial cMRI/MRS measurements will be performed in the trial, combining classical measurements as well as novel sequences and techniques.

Taken together, METAB‐HTX will allow a comprehensive analysis of the association of (a) glucometabolic and lipometabolic changes with (b) heart transplant events and (c) inter‐organ interaction with liver and renal deterioration. A combination of classical parameters as well as novel concepts including myocardial energy metabolism, novel cMRI/MRS analyses, cholesterol efflux and HDL function, leucocyte signatures, and thromboinflammation will be applied. METAB‐HTX will pave the road for specific novel marker and target identification as well as optimal planning of interventional trials to improve survival post‐HTX. It will allow further sub‐studies as well as nested‐randomized controlled trials.

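### The powered comparison groups patients by glucometabolic disease, which is also a component of the primary outcome being compared, so an association arises by construction

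*Protocol article*

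**What the plan says.** The primary endpoint (Abstract, Methods and results) is the incidence of heart transplant events. The list starts with ventricular function, allograft vasculopathy and rejection and ends with "worsening of kidney function, metabolic liver disease, infections, neoplasia, deterioration of glucose and lipid metabolism".

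The Study endpoints section confirms that the metabolic items belong to the composite. It opens with "Definitions of individual heart transplant event components are", and the list that follows includes "Glucometabolic disease will be defined as (i) impaired glucose tolerance" (with impaired fasting glucose and type 2 diabetes as alternatives) and "Lipid disease is defined as (i) elevating low‐density lipoprotein concentrations".

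The Sample size calculation restates the hypothesis that "metabolic deterioration post‐HTX is associated with impaired cardiac function and survival". It assumes that 60% of 400 patients develop glucometabolic disease after transplantation and that "the hazard for the primary outcome events is 35% higher (hazard ratio 1.35) in patients with glucometabolic disease". It gives a power of 0.8090 at alpha 0.05 and expects at least 100 outcome events. The Discussion plans the same kind of association, of "glucometabolic and lipometabolic changes with (b) heart transplant events".

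Cardiovascular and all-cause mortality, re-transplantation and ventricular assist device appear only after "Secondary outcomes include hospitalizations related to primary endpoints".

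**The concern.** The same named condition is on both sides of the powered comparison. Anyone who newly develops glucometabolic disease joins the exposed group and, at the same moment, has a primary event. The comparison would therefore show an excess in the exposed group even if glucometabolic disease had no effect on the graft, the kidney, the liver, infection or neoplasia.

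At stake is the meaning of the result for which the study is sized. A large and highly significant hazard ratio for the composite could not be told apart from the definition of the composite. A reader could take it as evidence that metabolic deterioration damages the transplanted heart.

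**Working it through.** **1. The plan's power figure.** Inputs from the Sample size calculation: N = 400, 60% exposed (ratio k = 0.6/0.4 = 1.5), HR 1.35, alpha 0.05. Sidedness is not stated; two-sided is assumed and reproduces the figure.

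Freedman's log-rank formula for unequal groups: power = Φ(√(E·k)·(HR − 1)/(1 + k·HR) − 1.96).

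With E = 400: √600 = 24.495; 24.495 × 0.35 / 3.025 = 2.834; 2.834 − 1.960 = 0.874; Φ(0.874) = 0.8090. This matches the stated figure, but only with one event per patient. Schoenfeld's formula, Φ(√(0.24·E)·ln 1.35 − 1.96), gives 0.8366 at 400 events and about 0.809 at 372 events (372/400 = 93% of patients). On either formula, nearly every patient must have an event.

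**2. Size of the overlap.** 0.60 × 400 = 240 patients are expected to develop glucometabolic disease. If all develop it during follow-up, 240 have a primary event by definition.

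**3. Hazard ratio with no true effect.** Assumptions: exposure treated as a fixed ever/never group; outcome is time to the first component; 60% exposed by 5 years; all other components independent of exposure. The article does not give the 5-year risk of the other components, so it is varied. Two onset patterns were simulated.

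| Assumed 5-year risk of other components | Composite HR, uniform onset | Composite HR, constant onset hazard |
|---|---|---|
| 25% | 12.3 | 13.4 |
| 50% | 4.6 | 5.1 |
| 70% | 2.7 | not tabulated |
| 75% | not tabulated | 2.7-2.8 |
| 85% | 1.95 | not tabulated |
| 93% | 1.58 | 1.8 |

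The true HR is 1.0 in every row and the planned HR is 1.35. With uniform onset and n = 400 (300 runs per row), a two-sided 5% test rejected in 99-100% of runs. With the glucose component removed and everything else unchanged, it rejected in 3-6% of runs and the HR was about 1.0. The excess therefore comes from the overlap.

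**4. Time-dependent exposure.** In a first-event analysis the onset of glucometabolic disease is itself the event and ends follow-up. A newly exposed patient contributes no exposed time at risk. The bias is replaced by a comparison that cannot be estimated for these patients.

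**5. Power once the component is removed.** The event count for a reduced composite is not in the article. At the only count it states, 100 events:
- Freedman: √150 × 0.35 / 3.025 − 1.96 = 1.417 − 1.960 = −0.543, power 0.29.
- Schoenfeld: √24 × 0.3001 − 1.96 = 1.470 − 1.960 = −0.490, power 0.31.
- HR detectable with 80% power (Schoenfeld): exp(2.80/√24) = 1.77.
- Events needed for 80% power at HR 1.35: 364 (Schoenfeld) or 391 (Freedman).

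**The case against.** The primary endpoint is worded as an incidence, and as a descriptive endpoint the full list is valid. The hypothesis concerns cardiac function and survival. The Introduction's aims relate metabolism to cardiac function, vasculopathy, infections, liver and kidney, and none of those outcomes contains the exposure. All of this stands, and it confines the problem to the association with the full composite. That association is the one the Sample size calculation powers.

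The article does not specify an ever/never first-event analysis, so the hazard ratios in the table are conditional on that assumption. The composite is also broad (any rejection above grade 0R or any infection needing professional intervention counts), so the upper rows overstate the likely size. Both points are fair. Even at 93% background risk, however, the artefact exceeds 1.35. An unseen analysis plan might soften the bias, for example with a recurrent-event model, but the endpoint, exposure and powered contrast are fixed here and conflict here.

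Some recruits come from the 250 recipients already transplanted (about 0.9 × 250 = 225 at the expected participation). Those with glucometabolic disease at entry need not count as having deteriorated. A reader should therefore not infer that every exposed patient has an event by definition; this holds for newly exposed patients.

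A reader might also infer that survival goes untested, or that patients who die are counted as event-free. The article supports neither: mortality is a named secondary outcome, and no text says how deaths are handled in the primary analysis.

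**Conclusion.** The powered comparison is circular as written, because glucometabolic disease is both its exposure and a component of its outcome. Under an ever/never first-event analysis with no true effect, the composite HR would be about 13 at an assumed 25% background risk and 1.6-1.8 at 93%, above the planned 1.35 across the range. With time-dependent exposure, newly exposed patients add no exposed time at risk. The sizes rest on the assumed background risk, onset pattern and fixed grouping; the overlap itself rests only on the text. Figure 1, which summarises the endpoints, was not available.

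The overlap is exact for glucometabolic disease only. Lipid disease is a component and part of the wider hypothesis of metabolic deterioration, but it is not the powered exposure. A reader might infer that every association in the study is true by construction; the organ-specific aims and the mortality outcomes remain free of this problem. The point should be corrected before the primary analysis is fixed, because a positive result for the composite could not otherwise be interpreted.

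**What to change.** For the hypothesis test and the power statement, define the outcome as the composite without the glucose component, and also without the lipid component wherever lipid change is the exposure. Keep the full heart transplant event list as a descriptive incidence endpoint.

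Restate the power for the reduced composite, with an expected event count and its basis, and reconcile it with the stated minimum of 100 events.

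Optionally, because the hypothesis names survival while neither the primary endpoint nor the power calculation includes it, add all-cause death and re-transplantation or ventricular assist device to the tested composite, or analyse them as competing events. They are already collected as secondary outcomes.

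No new data are needed. The cost is fewer events in the tested outcome and a less favourable power figure, possibly much lower than 0.8090 if the count is near 100.

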**Conclusions:**

The METAB‐HTX trial will identify early metabolic alterations potentially impairing cardiac function and outcome of HTX patients. This will identify patients at risk and allow precise planning of interventional trials to treat metabolic alterations post‐HTX and improve outcome.

## Introduction

Advanced heart failure occurs in up to 10% of heart failure patients with increasing prevalence.^1^ In these patients, heart transplantation (HTX) improves life expectancy from a median of 12.2 months to 12.2 years.^2^, ^3^ However, there is still a substantial need to improve long‐term survival post‐HTX. To address this need, an in‐depth understanding of factors that lead to worsening of cardiac function and mortality is needed. A recent analysis, investigating 30 606 post‐HTX patients, revealed an association of body mass index, type 2 diabetes (T2D), glomerular filtration rate, and bilirubin concentrations with mortality.^4^ Furthermore, it is known that T2D is frequent after transplantation with an incidence >20% within the first 2 years after transplantation.^5^ This can be partially explained by immunosuppressive therapy post‐HTX that is associated with incidence of T2D.^6^ Hence, it seems likely that metabolic alterations might be a crucial factor after transplantation. However, there are still many open questions. These include (i) an in‐depth understanding of the glucometabolic and lipid alterations over time post‐HTX, (ii) its association with cardiac metabolism and function as well as coronary allograft vasculopathy (CAV), (iii) its association with hepatic disease and renal function, and (iv) optimal timing and choice of treatment. To address these open questions, we conduct the METAB‐HTX trial. We hypothesize that metabolic deterioration post‐HTX is associated with impaired cardiac function and survival. The specific aims of the trial are (i) an in‐depth, time‐series analyses of glucometabolism and lipometabolism post‐HTX; (ii) association of changes in glucose and lipid metabolism with cardiac metabolism, function, CAV, and infections; (iii) association of glucometabolic and lipometabolic changes with hepatic and renal function; (iv) implementation of novel cMRI/MRS techniques to improve post‐transplant surveillance; and (v) evaluate the role of novel leucocyte signatures to predict malignant tumours and CAV as well as thromboinflammation patterns post‐HTX.

This trial will enable an in‐depth understanding of the association of metabolic deterioration, inter‐organ communication, cardiac function, and outcomes post‐HTX. It will pave the road for identification of specific novel therapeutic targets and precise planning and conduction of interventional trials to improve outcome post‐HTX.

## Methods

### Study design

METAB‐HTX is a prospective, longitudinal cohort study. The study will be initiated in the University Hospital Düsseldorf with the option to include further centres (for sub‐studies) to gain extern validation in the future. The study is approved by the Institutional Ethics Committee (Medical Faculty, Heinrich Heine University, Düsseldorf) in accordance with the World Medical Association Declaration of Helsinki. Written consent prior inclusion is required (reference numbers 5263R, 2021‐1635, and 2022‐1962).

### Study population

Patients on the heart transplant waiting list as well as post‐HTX patients will be included. Inclusion criteria will be age >18 years and planned or already conducted HTX. In cases of temporal inability to decide for or against a participation, the patient's legal guardian will be asked for consent provisionally. Exclusion criterion will be the absence of informed consent.

### Study endpoints

The primary and secondary endpoints are summarized in *Figure*
*1*. Definitions of individual heart transplant event components are:

**Figure 1 ehf215330-fig-0001:**
[figure not shown]
Study endpoints.

Worsening of systolic or diastolic left ventricular function is defined by occurrence or progression of diastolic or systolic dysfunction measured by cMRI or echocardiography. Worsening of systolic function is defined as reduction of LVEF of at least 10% or a relative reduction in GLS of at least 15%. Worsening of diastolic function is defined as new onset of increased grading of diastolic dysfunction according to the guidelines for diastolic function in HTX patients.^7^ Furthermore, any adverse remodelling in myocardial texture and myocardial T1/T2 relaxation times will be documented as heart failure event.

CAV grading will be performed according to the current ISHLT guidelines as previously described, with ISHLT CAV 0 indicating no significant CAV, ISHLT CAV 1 defined as mild CAV, ISHLT CAV 2 as moderate CAV, and ISHLT CAV 3 as severe CAV.^8^, ^9^, ^10^ Every diagnosis of ISHLT CAV > 0 and every progression in CAV grading constitutes a heart transplant event.

Cellular rejection will be defined using the Revised ISHLT Grading Scale, which categorizes rejection from grade 0R (no rejection) to grade 3R (severe rejection) based on the degree of mononuclear cell infiltration and associated myocyte damage in endomyocardial biopsies. Humoral rejection, or antibody‐mediated rejection (AMR), is evaluated based on histopathologic and immunopathologic criteria, including evidence of microvascular injury, complement deposition (C4d staining), and circulating donor‐specific antibodies (DSA). AMR is classified as pAMR 0 (no AMR), pAMR 1 (suspected AMR), or pAMR 2 (definite AMR) according to biopsy findings and serologic markers. Any rejection diagnosis of >ISHLT G 0R or >pAMR 0 constitutes a heart transplant event.

Worsening of kidney function will be determined by eGFR mean slope change [mL/min/1.73 m^2^] as well as classification of acute kidney injury according to KDIGO criteria (creatinine increase 0.3 within 48 h/1.5‐fold change within 7 days).

Liver disease will be defined by occurrence of structural liver disease according to current guidelines^11^ or increase of liver plasma enzyme concentrations.

Infections requiring healthcare professional interventions will be defined as heart transplant event.

Neoplasia is defined as first diagnosed and histopathological confirmed solid or non‐solid malignant tumours.

Glucometabolic disease will be defined as (i) impaired glucose tolerance (2‐h glucose levels of 140–199 mg per dL on the 75‐g oral glucose tolerance test), (ii) impaired fasting glucose (fasting plasma glucose values of 100–125 mg per dL), or (iii) diagnosis of T2D according to current criteria of the American Diabetes Association.^12^

Lipid disease is defined as (i) elevating low‐density lipoprotein concentrations, apolipoprotein B concentrations, and fasting triglyceride levels; (ii) impaired HDL function; (iii) enhanced membrane fluidity; or (iv) membrane cholesterol enrichment in time‐series analyses.

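### Several primary-endpoint components (eGFR slope, liver enzymes, T1/T2 and texture, lipids) are not defined as dated, thresholded events, although the endpoint is powered on a hazard ratio

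*Protocol article*

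**What the plan says.** The abstract states: "The primary endpoint will be the incidence of heart transplant events". The Study endpoints section then introduces the component rules with "Definitions of individual heart transplant event components are", so what follows is the article's own definition of the primary endpoint. The components at issue are:

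- **Kidney:** "Worsening of kidney function will be determined by eGFR mean slope change", paired with acute kidney injury by KDIGO criteria.
- **Liver:** structural liver disease by guideline, "or increase of liver plasma enzyme concentrations".
- **Myocardium:** "any adverse remodelling in myocardial texture and myocardial T1/T2 relaxation times will be documented as heart failure event".
- **Lipids:** (i) "elevating low‐density lipoprotein concentrations, apolipoprotein B concentrations, and fasting triglyceride levels", or ("ii) impaired HDL function; (iii) enhanced membrane fluidity; or (iv) membrane cholesterol enrichment", judged over time.

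The neighbouring components have usable rules. LVEF must fall by at least 10% or GLS by at least 15% relative. CAV counts above ISHLT grade 0 or on progression, and rejection counts above 0R or pAMR 0. AKI has a creatinine rule, and the glucose categories have mg/dL limits.

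The Sample size calculation section assumes 400 patients, 60% with glucometabolic disease, a hazard ratio of 1.35 for primary outcome events and alpha 0.05. It reports power of 0.8090. It also expects at least 100 outcome events.

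**The concern.** A hazard-ratio analysis needs, for each patient, a date on which a defined state was first met. A mean slope change has no such date and no cut-off, so it cannot enter the composite as a patient-level event.

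The liver, T1/T2 and texture, and lipid components could be events, but nothing in their definitions separates a meaningful change from ordinary variation between visits. Applied literally, they could be met by patients in whom nothing has changed, whatever their metabolic status. In a first-event composite, such an event also ends the patient's time at risk before a later CAV, rejection or ventricular event can count. The contrast between patients with and without glucometabolic disease then shrinks towards 1 while the event count looks reassuringly high.

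**Working it through.** **Step 1. Reproduce the stated power.** The inputs come from the Sample size calculation section: hazard ratio 1.35, 60% exposed (ratio φ = 0.6/0.4 = 1.5) and alpha 0.05, taken as two-sided because the sidedness is not stated. Freedman's formula for D events is

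power = Φ( √(D·φ) · |HR − 1| / (1 + φ·HR) − 1.96 ).

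With D = 400: √600 × 0.35 / 3.025 = 2.834, and Φ(2.834 − 1.96) = 0.809. This matches the stated 0.8090. The match needs 400 events in 400 patients, so the figure corresponds to every patient having a primary event. With the 100 events given as a minimum in the same section, the same formula gives 0.29. It needs 391 events for 80% power.

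**Step 2. How often would an unqualified rise occur by chance?** The article gives no within-patient variability, so this step rests on assumptions: a stable patient, symmetric normal visit-to-visit noise, and any rise above one baseline value counting. Table 1 schedules AST/ALT, GGT and AP at listing, post-transplant, 1, 3 and 5 years. That gives four enzymes and, from a post-transplant reference, three later visits.

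- Independent enzymes, one visit: 1 − 0.5⁴ = 94%.
- Independent enzymes, three visits: each baseline is the highest of four exchangeable values with probability 1/4, so 1 − (1/4)⁴ = 99.6%.
- Between-enzyme correlation 0.7 (simulated): 73% at one visit, 92% over three.

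The size of the noise does not matter here, because any rise counts. A limit changes the picture. If the rise must exceed the 95% reference change value (2.77 within-patient SD), the three-visit figure falls to 17–23% for correlations 0.6 to 0. Without a limit it is 94–99.6% over the same correlations.

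**Step 3. What would dilution do?** Suppose a share f of events has no relation to exposure (hazard ratio 1). Then approximately HR = 1.35·(1 − f) + f. With 400 events and the formula of Step 1:

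| f | HR | Power |
|---|---|---|
| 0 | 1.35 | 0.81 |
| 0.25 | 1.26 | 0.60 |
| 0.50 | 1.18 | 0.34 |
| 0.75 | 1.09 | 0.13 |

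The values of f are scenarios. They are not derived from Step 2, and the article contains nothing from which to estimate f.

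**The case against.** The strongest reply is that this is a condensed article. Limits, reference visits and adjudication rules often sit in the full protocol or analysis plan, and the endpoint figure is not visible. The enzyme sentence does not say that any rise above baseline counts. It defines liver disease, so it could mean values above the reference range, and the lipid wording could be read the same way. That stands as a limit on Step 2, which illustrates one reading. It does not remove the point. The article chose to define the components and gave limits for most of them, and no reading turns a mean slope into a dated event.

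Other parts of the reply also stand:

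- The kidney component includes KDIGO AKI, which is a proper event. Only the slope half fails.
- The imaging sentence is restricted to adverse remodelling and speaks of a heart failure event, not a heart transplant event. Whether it counts toward the composite is therefore unclear.
- The Introduction plans separate associations with cardiac function, CAV, infections, liver and kidney. A real effect on one component is not lost to the study even if the composite is diluted.

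A reader might infer from Table 1 that the lipid criteria cannot be applied, because it omits apolipoprotein B, HDL function and the membrane assays. The article does not support that: the Systemic phenotyping section plans all of them. A reader might also infer that noise is bound to dominate the primary endpoint. That does not follow either, because neither component rates nor within-patient variability are given.

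**Conclusion.** The point holds as a defect in how the primary endpoint is fixed. One element, eGFR slope, cannot be part of a time-to-event composite under any reading. Three others (liver enzymes, T1/T2 and texture, lipids) lack the limit, reference visit and confirmation that would make them reproducible patient-level events, and whether the imaging findings count is itself unclear.

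The possible loss is large: power between about 0.60 and 0.13 for unrelated shares of 25% to 75%. That range is conditional on 400 events, a hazard ratio of exactly 1 for the unrelated events, and shares that the article does not let anyone estimate. The chance-rise figures of 73–99.6% hold only if any rise above baseline counts. Both sets of numbers show why the wording matters; neither predicts the trial's result.

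**What to change.** 1. **Kidney.** Take eGFR slope out of the composite and analyse it as a separate continuous outcome in a mixed model. Keep AKI as the kidney event and, if wanted, add a confirmed relative eGFR fall of stated size from a post-transplant reference value.
2. **Liver enzymes and conventional lipids.** Fix a limit in advance, for example a multiple of the upper limit of normal or the reference change value, with a named reference visit and confirmation on repeat. These are examples of form; the sponsor should choose and justify the values.
3. **T1/T2 and texture, HDL function, membrane fluidity and membrane cholesterol.** State whether each counts toward the primary composite. If it does, fix a limit; if not, report it as secondary or exploratory.
4. **Power.** Recalculate it on the event rate that the revised composite is expected to give, and state the number of events assumed.

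This changes wording and needs no new measurements. The cost is fewer primary events, and Step 1 shows how much that matters: the stated power already corresponds to an event in every patient.

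### The glucometabolic component is defined by presence of dysglycaemia, with no new-onset or progression rule, so disease carried over from before transplantation counts as a post-HTX event and as exposure

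*Protocol article*

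**What the plan says.** The Abstract sets the endpoint as a count of new happenings: "The primary endpoint will be the incidence of heart transplant events". It lists among the components "deterioration of glucose and lipid metabolism". The hypothesis likewise concerns metabolic worsening after transplantation.

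The Study endpoints section introduces its list as the definitions of the individual event components. For glucose it reads: "Glucometabolic disease will be defined as (i) impaired glucose tolerance" (2-h value 140–199 mg/dL), or impaired fasting glucose (100–125 mg/dL), or "diagnosis of T2D according to current criteria of the American Diabetes Association". All three describe a current state.

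Two other components are worded differently. For coronary allograft vasculopathy, "every progression in CAV grading constitutes a heart transplant event". For malignancy, "Neoplasia is defined as first diagnosed and histopathological confirmed".

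The Sample size calculation uses glucometabolic disease as the exposure and assumes that "60% of patients develop glucometabolic disease after HTx". With 400 patients, alpha 0.05 and a hazard ratio of 1.35 it reports power of 0.8090.

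Under Study population, waiting-list and already transplanted adults are both eligible, and lack of consent is the only exclusion. Table 1 schedules OGTT, fasting glucose, HbA1c and medical history at listing (V1).

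**The concern.** A rule that asks whether dysglycaemia is present cannot measure whether it appeared or got worse. Nothing keeps patients with existing dysglycaemia out of the cohort, so long-standing disease enters both the event count and the exposed group alongside disease that arose after transplantation. The resulting incidence would partly be prevalence. The hazard ratio would mix the effect of pre-transplant diabetes with the effect of post-transplant deterioration, and only the second is the study's hypothesis. Two analysts working from the same data could also reach different event counts, one following the component definition and the other the incidence wording.

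**Working it through.** **1. Apply the rule as written to typical patients.**

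| Before HTX | After HTX | Result under the definition | Did glucose metabolism deteriorate? |
|---|---|---|---|
| T2D | T2D, unchanged | Event and exposed | No |
| T2D | T2D, worse control | Event and exposed; no higher category exists | Yes, but not distinguished from the row above |
| IFG/IGT | IFG/IGT persists | Event and exposed | No |
| IFG/IGT | Normal | Neither | No |
| IFG/IGT | T2D | Meets a further criterion, but no rule makes it a new event | Yes |
| Normal | IFG/IGT or T2D | Event and exposed | Yes |

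The rule matches the stated aim in the fourth and last rows. It gives a wrong result in rows 1 and 3 and fails to separate real worsening in rows 2 and 5.

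**2. Already transplanted patients.** The Sample size calculation gives a pool of 250 living recipients and 90% participation: 250 × 0.90 = 225, and 225/400 = 56%. Up to about that share enters after transplantation and has no study assessment at listing. Under the definition, dysglycaemia at their enrolment scores whenever it began.

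**3. Reproduce the stated power.** Inputs from the Sample size calculation: N = 400, 60% exposed, HR 1.35, alpha 0.05 (sidedness not stated; two-sided used). With Freedman's log-rank formula and k = exposed/unexposed = 0.6/0.4 = 1.5:

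power = Φ( √(E·k) × (HR − 1) / (1 + k·HR) − 1.96 )

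With E = 400 events: √600 × 0.35 / 3.025 = 2.834; 2.834 − 1.96 = 0.874; Φ(0.874) = 0.8090. The figure reproduces, so there is no arithmetic slip here. It requires an event in every patient. That is a separate matter and is held fixed below.

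**4. Illustrate sensitivity to prevalent disease.** The article gives no prevalence p at listing, so 10–50% is an assumption. Suppose patients with dysglycaemia at listing leave the risk set, so that E = 400(1 − p). Case A: 60% of those remaining develop disease (k = 1.5). Case B: the 60% already includes prevalent cases, so k = (0.6 − p)/0.4.

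| Assumed p | 400 × p | At risk | Power, case A | Power, case B |
|---|---|---|---|---|
| 10% | 40 | 360 | 0.767 | 0.789 |
| 20% | 80 | 320 | 0.717 | 0.759 |
| 30% | 120 | 280 | 0.660 | 0.712 |
| 40% | 160 | 240 | 0.593 | 0.629 |
| 50% | 200 | 200 | 0.518 | 0.456 |

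Example, case A at 10%: √(360 × 1.5) × 0.35 / 3.025 − 1.96 = 0.729; Φ(0.729) = 0.767.

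The second column is the most that could be miscounted at each assumed prevalence, since some IFG/IGT resolves. Removing these patients altogether is harsher than the fix below, which keeps them and stratifies.

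**The case against.** The best defence is that the passages should be read together: the Abstract supplies incidence and deterioration, the Sample size calculation speaks of disease arising after transplantation, and the component definition only supplies thresholds. Handling of prevalent cases might then sit in a fuller document, and Figure 1 is not shown. This has some force, but no sentence says that only new cases count. The section that sets out to define the event components gives a complete rule that yields a different answer. That is a stated rule in conflict with its purpose, not merely an omitted detail.

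Four limits on the point do stand.

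- A reader might infer that everyone with dysglycaemia at listing becomes an event automatically. That is not supported: a criterion must still be met after transplantation, and IFG/IGT may have resolved. It does apply to an established T2D diagnosis.
- A reader might infer that such patients can never show later worsening. That is not supported either: T2D is a separate listed criterion that a patient with IFG/IGT can newly meet, and serial OGTT, HbA1c and insulin-resistance indices are scheduled. What is missing is a rule that makes the move an event.
- One might divide an assumed prevalence by 60% to say how much of the exposed group is pre-existing disease. The article describes the 60% as developing after transplantation, so prevalent cases cannot simply be placed inside it.
- The baseline question is not peculiar to glucose. The vasculopathy component also counts any grade above 0, so already transplanted patients raise it there too.

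**Conclusion.** The point holds in this form. The glucometabolic component is defined by presence, in conflict with the article's own incidence and deterioration wording and with the exposure described in its power calculation. T2D at listing, and IFG/IGT that persists, is counted as a post-HTX event and as exposure. A move from IFG/IGT to T2D has no rule making it a new event, and patients with T2D at listing have no higher category to reach.

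The number of patients affected cannot be derived from the article. The power range of about 0.77–0.52 (case A) or 0.79–0.46 (case B) rests on an assumed listing prevalence of 10–50%, on removing prevalent patients from the risk set, and on keeping the implicit assumption of 400 events. It shows that the choice matters; it does not estimate the loss. The definition should be corrected, because it changes what the main hazard ratio estimates.

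**What to change.** Define the component and the exposure as new onset or a step up in category (normal to IFG/IGT, or either to T2D) against a named reference:

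- **Patients enrolled at listing:** the pre-HTX state from the V1 OGTT, fasting glucose, HbA1c and medical history.
- **Already transplanted patients:** documented pre-HTX history. Where this is lacking, classify dysglycaemia at enrolment as prevalent with unknown onset, and count only step-ups after enrolment as incident. The enrolment test is a post-HTX value and should not stand in for the pre-HTX state; using it that way would relabel true post-transplant diabetes as pre-existing.

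Stratify the main analysis by pre-HTX or baseline glucometabolic status, and report patients with T2D at baseline separately.

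For patients enrolled at listing the data are already scheduled, so the cost is wording and one stratification factor. For up to about 225 already transplanted patients it also means extracting records. Fewer glucometabolic events and a smaller newly exposed group will result, so the 60% assumption and the power of 0.8090 should be rechecked and restated under the revised definition.
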